## Methods

Using the ROIO design, we will engage our CARAB to refine and optimize implementation of the I-FRESH program before and after each roll-out in 4 clinics at Rady Children’s Health in San Diego: diabetes, gastroenterology, preventive cardiology, and severe asthma clinic. Periodic Reflections [34] will be held before, during, and after implementation in each of the 4 clinics with CARAB to determine which refinements or adaptations should be made to increase adoption and improve implementation of this workflow. Using the PRISM framework, this group will identify factors in the inner and outer context that serve as barriers and facilitators to I-FRESH implementation and family engagement in the program (Aim 1). Using Implementation Mapping [35] processes, we will refine an effective implementation process model for our healthcare system. We will also assess implementation outcomes of the I-FRESH program using the RE-AIM outcomes framework [32, 33] (Aim 2). Finally, we will examine preliminary effect on family-level food security and pediatric nutrition-related health outcomes (Aim 3). The I-FRESH study was approved by the UC San Diego IRB (protocol # 810869).

### Setting and context

Participants will be drawn from the 4 clinics at Rady Children’s Health in San Diego, a comprehensive pediatric healthcare system serving more than 91% of the children and adolescents (>900,000 youth) in San Diego County (5th largest county in the U.S.), Imperial, and Riverside Counties. In 2022, 22.7% of residents living in San Diego County were below 200% of the Federal Poverty Level (FPL) [36]. Community health assessments conducted by the public health departments of San Diego and Riverside counties identified that low-income households have insufficient resources to buy adequate fruits and vegetables (FV) [37, 38], and 37% to 45% of low-income families with children (<200% of the FPL) have FI [38, 39]. Rady Children’s Health uses Epic^©^ as their electronic health record (EHR), and the 2-item Hunger Vital Sign [40] was implemented in 2020. The health system has a SDOH workgroup that consists of physician champions, Information Technology (IT) experts, dietitians, social workers, and members of the Population Health department. This workgroup assists in making changes in Epic^©^, creating decision support tools, and addressing other hospital-wide procedures and regulations that hinder or assist efforts to identify and address SDOH needs of the patients.

### Participants

Members of the CARAB (which includes health care providers, hospital administrators, population health/public health leaders, staff from community-based organizations (CBOs), food as medicine experts, equitable food systems collaborative leaders, community members, community health workers, and the research team) will be invited to provide their views and opinions on how the program is functioning and complete RE-AIM assessments. Our goal is to recruit up to 100 health care staff and CARAB stakeholders to complete Aims 1 and 2. Up to 10 parent participants per clinic (*n* = 40) who are 18 years or older will also be asked to participate in Aims 1 and 2. These parents/caregivers will have a child with a nutrition-related condition who attends one of the 4 participating clinics and screens positive for FI.

To study the impact of this program on family-level FI and pediatric nutrition-related health outcomes (Aim 3), we plan to recruit 240 parents of a child aged 0–18 attending one of the participating clinics (~60 per clinic). These families will screen positive for FI based on the 2-item Hunger Vital Sign [40].

Exclusion criteria will be limited given the heterogeneous nature of the populations in each clinic. This will increase generalizability of our findings and allow us to explore a wide range of implementation issues before testing this program in a larger type 2 hybrid effectiveness-implementation trial. We will track the following variables and include them as covariates or moderators rather than exclusion criteria: 1) child medical conditions for which physician supervision of diet are needed; 2) child body mass index (BMI) percentile; 3) child medications; 4) family language preferences; 5) family household size and composition; and 6) other SDOH factors (e.g., lack of housing or transportation) that would impact the family’s ability to access nutrition support programs.

### Study objectives

#### Specific Aim 1: Refinements and adaptations: implementation Mapping

The goal for Aim 1 is to identify which components of the I-FRESH intervention and implementation strategies are effective and which intervention components and implementation strategies need to be modified to increase the impact of I-FRESH for different populations in different clinic settings. This information will help to identify which program components and implementation strategies are key to program success and should be prioritized when implemented across diverse settings and external contexts. We will use the Implementation Mapping [35] approach to develop expected implementation outcomes for the RE-AIM domains of adoption, implementation, fidelity, and maintenance.

Prior to the first roll-out, we will engage CARAB and other key stakeholders to participate in a brainwriting premortem [41] discussion to refine the program structure and identify potential barriers and facilitators to implementing the full workflow. During this this co-production process [42], participants with expertise in implementation science, clinical informatics, behavior change, and historical evidence behind implementing such a program will be able to discuss with those who have detailed knowledge of the logistics of implementing such a program in the hospital and its EHR, and those who have expertise around the community/family perspectives and context. During this process, modifications to implementation strategies, program content, format of delivery, and timing of program components will be made as needed. Barriers to optimizing fidelity and reach (be it from the internal or external context/environment) will be identified, documented, and addressed when possible. Program materials and protocols will be adapted to foster multiple levels of communication and information sharing between families, the health system, and community programs. Finally, existing materials, referrals, and resources will be modified to make them more user friendly for the English and Spanish-speaking populations. Members of the CARAB will provide input on all these modifications and review program materials before they are implemented.

Once the program is implemented in each clinic, we will conduct periodic reflections [34] with key stakeholders, including families, and the CARAB to allow for real-time iterations in program implementation. These reflections will occur before, during, and after roll-out of the intervention in each of the 4 clinic sites. Roll-outs in each new clinic will occur every 4 months. We will use a modified Stirman Framework [43] to track adaptations monthly [44]. Documentation of adaptations will include brief multilevel surveys with staff and key stakeholders. Semi-structured interviews or focus groups with key stakeholders and families will occur at 3 and 6 months to expand on written adaptations. Data from all sources will be triangulated using joint display analysis [45] to determine which adaptations should be included as permanent implementation strategies in the next clinic iteration

**Proposed I-FRESH workflow and implementation strategies:**

The I-FRESH workflow includes: 1) Screening and Identification; 2) Readiness assessment, 3) Referrals; 4) Follow-up regarding access, utilization, and fit of referral service. (Fig. 2)

##### Screening and identification

The first step in this process is to identify FI through regular surveillance and screening with validated screening tools [46]. We plan to use the EHR to implement the screening tool because it has been shown to improve SDOH reporting compared to in-person assessments that may occur in the presence of children or other family members, and lead to shame or embarrassment [47–49]. However, this strategy may need to be refined to include reminders or prompts if the screener has not been completed. This process also assumes that families are interested in receiving help in this domain [25, 50]. Some families may have other priorities that need to be addressed first [26, 51]. Other families may not report FI status because of concerns that information is being shared with law enforcement or government agencies [26, 51]. Families may also fear discrimination from healthcare providers for being identified as having FI and carry their own personal shame around these issues [52]. For these reasons, we will engage with CARAB and other key stakeholders in the healthcare system to develop a process where family/patient needs and interests are reviewed in a manner that allows for personal autonomy and is responsive to their current situation. Before each roll-out, we will educate the healthcare team on this newly refined process. An EHR registry will also be created to track families who have screened positive for food insecurity to facilitate next steps in the screening and referral process.

##### Readiness assessment

In-person assistance with referrals and resource navigation has been shown to result in higher contact or follow-up with identified services [53]. Therefore, discussions with the health care provider (physician, nurse practitioner, nurse) or social worker, care navigator, or community health worker will be included to allow for assessment around urgency of need and readiness to utilize community support programs. It also provides an opportunity to address concerns or questions about the referrals. The EHR registry will be used to track which families need additional follow-up or care navigation. However, refinements to this implementation strategy may be needed to determine which members of the healthcare team will conduct this follow-up and track the family’s progress. Ultimately, linking these conversations (which would include a shared decision-making model and trauma-informed lens [24, 54]), with the screening process may facilitate enrollment into nutrition support programs [55]. These conversations will also allow the health care provider and/or allied health professional to assess the patient or family’s assets and strengths [56–58], and highlight them as tools to mitigate risk.

##### Referrals

In addition to developing a robust screening and identification process, it is important to identify relevant resources to address discovered SDOH needs. Screening without offering assistance may cause distress for both affected families and health care providers, resulting in a failed program. Some families may not reveal they have SDOH needs unless resources are provided [50, 59], or there is some indication that services are available if needed. Thus, in our program, we plan to inform families there are resources available for those who are interested before they complete the FI screener. We plan to develop a repository of community resources that is available to staff and families in the EHR and on the health system website. Refinements will need to be made to determine the best strategies to increase staff and family awareness of these resources.

##### Follow-up: access, utilization, and fit of referral service

After the initial referral, care coordinators will follow-up with families within 2–4 weeks to obtain feedback regarding the programs or CBOs they accessed, and problem-solve any challenges. This workflow is based on prior best practice we developed with the San Diego County 211 program. However, we will need to determine which strategies to utilize to implement this component of the intervention. Local consensus discussions may need to occur to determine how feasible this is. During this follow-up call, it is proposed that care coordinators will determine whether families contacted the program and if they encountered any barriers. They will also collect feedback about the CBO program and identify if there are other needs. Additional referrals will be made if needed. Depending on the feedback received during the implementation and adaptation process, this component may be repeated every 2–4 weeks until families no longer require the help of the care coordinator.

#### Specific Aim 2: Assess implementation outcomes

With each iteration of the roll-out, we will gather implementation outcomes from each level of the program: individual/family, hospital, and community partner level. Using the RE-AIM outcomes framework [32, 33], our primary implementation outcomes are feasibility and acceptability of I-FRESH by families, healthcare providers, ancillary support staff, administrators, community nutrition support programs, and community members. We will also assess fidelity, adoption, and reach of the program by assessing which components were carried out by ancillary health care staff/care navigator, staff/setting characteristics, and percentage of families who participated. Reach and maintenance of the program will be tracked through the EHR registry. (Further details on assessments are presented below in Measures.)

#### Specific Aim 3: Examine preliminary impact and effectiveness outcomes

We will further apply RE-AIM and examine exploratory clinical effectiveness outcomes including family-level FI and pediatric nutrition and metabolism-related health outcomes that may be similar across the different clinics: weight status, blood pressure (BP), lipids, HbA1c, and liver function tests. We will also assess changes in medication dose or type (e.g., stopping insulin and only requiring metformin) and engagement with the clinic or recommended services (e.g., decrease in no-show rates). While the larger goal of the program is to decrease FI and improve health outcomes, we will also collect information on the family’s self-reported knowledge, skills, attitudes (expectancies), self-efficacy, and social support needed to engage in the program. Other behaviors of interest include consumption of and barriers to consuming fruits and vegetables.

### Measures: (Table 1)

#### Implementation adaptations and outcomes (Aims 1 and 2)

We will use several data collection methods to capture the adaptations made to the implementation strategies (Aim 1), such as the modified Stirman adaptation framework and coding system [44, 69] to track refinements that occur. We will ask clinic staff and other hospital or program-related staff to record any adaptations that have been or need to be made in program content or delivery. Then we will review this in CARAB meetings where periodic reflections [34] will occur to determine if iterative refinements need to be made to the program before the next roll-out. These reflections will code the who, how, what, when, and why the adaptation was made, and barriers or facilitators (program determinants) to program implementation. These reflections should address the following questions (among others): What are the contextual contingencies that would make this program implementation more successful, what resources (e.g., personnel, IT support) are needed to successfully implement this program, what adaptations to the workflow need to be made, how willing is the current workforce to make these adaptations, how can we fit the program workflow into current contextual workflows? Additionally, semi-structured interviews will be conducted with multiple family, community, clinical, and hospital level stakeholders to determine if other refinements should occur and the perceived importance of these and other previously identified modifications. We will use the FRAME-IS [70, 71] (which assesses what types of adaptations were made and why) as prompts for these interviews/meetings and review any immediate changes needed at the research team and CARAB meetings. Solutions to the identified barriers will be co-created during these meetings.

**Table 1 Tab1:** Assessments for each Aim and level (family, healthcare system, community program)

	Assessments	Parent (P), Child (Ch), Healthcare (H), Community (Com)	Data type & source	Frequency of assessment
Aim 1 Implementation Mapping and Optimization	• Adaptations and Implementation strategies • Barriers to program implementation • Structures and systems needed to implement program and support community programs • Experience with multi-component implementation • PRISM Fit assessment	H, Com H, Com H, Com P, H, Com P, H, Com	Periodic reflection, Interviews Periodic reflection, Interviews	Before, during, after each roll-out Before, during, after each roll-out
Aim 2 Implementation Outcomes	• Acceptability, Feasibility, Appropriateness of program [60] • Reach: % of families attending clinic that completed screener, # of families in the registry, % of families that did not want service, Characteristics of participating vs. non-participating families • Adoption: Characteristics of clinic settings and staff, Characteristics of community program (location, months/days/hours of operation, description of benefits or incentives, educational programs available) • Readiness for organizational change scale [61] • Implementation Climate Scale [62] • Implementation/Fidelity: % of families that were called, % of families that were referred or provided with resources, % of families that received follow-up phone calls, % of families that needed additional resources/referrals • Maintenance: • Program Sustainability Index [63] • Perceived support of innovation in organizations [64] • Partnership synergy tool [65–67]	P, H, Com H H, Com H H, Com	Periodic reflection, Interview, Survey EHR, Survey Survey, Periodic reflection EHR, Periodic reflection Survey	6, 12 mos Ongoing & 12 mos Ongoing & 12 mos Ongoing & 12 mos 12 mos
Aim 3 Effectiveness Outcomes	• Health outcomes: BMI/weight status, HbA1c, blood pressure, total cholesterol, HDL cholesterol, liver function, health status • Quality of life, stress, well-being • PRAPARE (patient assets, risks, and experiences) • Medications (including dose) & Health care utilization • Community program utilization (including barriers & facilitators) • Knowledge, Skills, Attitudes, Self-efficacy • Food Frequency Questionnaire [68] • Demographics: Race/ethnicity, age of child and parent, sex and gender identity of child and parent, address, zip code, birthplace, current employment status, educational attainment, annual family income, health insurance • SDOHfactors: Food insecurity, health literacy & numeracy, access to health services, access to health technology, internet access, job insecurity, housing insecurity, discrimination, discrimination in health care, food swamp	Ch P P Ch P P P P, Ch P	EHR Survey Survey EHR Survey Survey Survey Survey, EHR Survey	0, 6, 12 mos 0,12 mos 0,12 mos 0,12 mos 0,12 mos 0, 6, 12 mos 0, 6, 12 mos 0 mos 0, 12 mos

The PRISM Fit Assessment [72–74] will be conducted before each new roll-out of a clinic which examines how well the current implementation strategies align with the new clinic and whether it will reach similar RE-AIM metrics as in the previous clinic implementation. Representative clinic providers and staff, community stakeholders and hospital administrators will complete this 21-item survey using the iPRISM web tool (prismtool.org) before each clinic roll-out. Results will be reviewed during a CARAB meeting and additional refinements to the implementation strategy will be made.

Using the RE-AIM framework [32, 33], we have identified several implementation outcomes to assess (Aim 2). These variables include reach, adoption, maintenance, acceptability, appropriateness, and feasibility of implementation strategies. We will be able to track reach and maintenance of the program through the registry we create in the EHR. All patients attending the participating clinics will be included in the registry, and we will be able to track what proportion completed a FI screener, and what proportion screened positive for food insecurity. This data can be visualized in a dashboard and used to provide feedback to key stakeholders until it is disabled. To better understand factors from the external and internal context that support implementation and adoption, we will assess the readiness of the health care setting, community-based organizations (CBOs), and individuals participating in this program. Finally, characteristics of the health care setting, community programs, and families that increase and decrease the likelihood that adopting this food security referral program model will be assessed.

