The specific aims of this study are:To engage our Community, Clinical, Administrative, and Research Advisory Board (CARAB) to *refine and optimize* the program before and after each roll-out in 4 clinics and identify factors in the inner and outer context that serve as barriers and facilitators to engaging in the program.To assess *implementation outcomes* of our comprehensive nutrition support program and determine:*Feasibility and acceptability* of I-FRESH by families, healthcare providers, ancillary support staff, administrators, community nutrition support programs, and community members, and*Fidelity, adoption, and reach* of the program by assessing which components were carried out by ancillary staff/care navigator, staff/setting characteristics, and percentage of families who participated.To examine *preliminary effectiveness outcomes* on family-level FI and pediatric nutrition-related health outcomes, such as, weight status, blood pressure, lipids, HbA1c, and liver function tests. We will also assess changes in medication dose or type (e.g., stopping insulin and only requiring metformin) and engagement in recommended services (e.g., decrease in no-show rates).

We hypothesize feedback and adaptations will develop an implementation bundle that is feasible and acceptable to families, staff, healthcare providers, hospital administrators, and community nutrition support programs. Our goal is to have a robust, feasible, and scalable program that can be tested in a fully powered Type 2 Hybrid Effectiveness-Implementation Trial.

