#### Medical record abstraction

EHR data will be used to track preliminary clinical effectiveness outcomes (Aim 3). EHR data will be used to track patient health outcomes (e.g., BMI, HbA1c, LFTs, cholesterol), SDOH outcomes, medication adherence, health care utilization (e.g., follow-up visits made to primary care or subspecialty physicians, adherence to appointments, ED visits, hospitalizations, lab orders, medications prescribed), and I-FRESH program process measures (e.g., phone call attempts by the care navigator, referrals made to community nutrition support programs). Demographic information (i.e., age, sex, race, ethnicity, insurance status) will be collected to examine if there are differences between those who engage in the program and those who do not.

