#### Quantitative data

Primary analyses for Aim 2 will assess fidelity and reach outcomes (Aim 2b) assessed within the EHR (e.g., screening, referrals, and follow-up assessments) and surveys (e.g., Acceptability, Feasibility, and Appropriateness) across the study period using Generalized Linear Mixed-effects Models (GLMM) and time-varying indices for clinics randomized to cross-over in each wave, time (secular trend), and clinic characteristics as planned covariates. Serial cross-sectional summaries for each clinic within monthly blocks will allow estimation of changes in clinic outcomes after crossing over into interventions. Primary analyses for Aim 3 will describe I-FRESH participants’ (*n* = 240) changes in health outcomes including: a) metabolic labs, BP, BMI, b) healthcare utilization; c) community program utilization; d) Quality of Life; e) Food Frequency Questionnaire and f) Knowledge, Skills, Attitudes, and Self-Efficacy. GLMM growth models for individual trajectories of continuous and limited categorical outcomes will include a focus on significance of changes from baseline to post-treatment assessments after graphically examining an appropriate functional form (e.g., linear or categorical) for modeling each outcome. All models will include participants’ characteristics (gender, ethnicity, parental education) and allocation clinic as planned covariates when estimating changes in primary health and engagement outcomes. We will explore the role of SDOH and implementation strategy effectiveness as potential influences in describing changes in parent and child health outcomes. Benjamini-Hochberg [78] procedures will be used to adjust *p*-values for inference decisions within common domains.

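### Total cholesterol contains HDL, so as a separately tested Aim 3 outcome it understates a non-HDL improvement whenever HDL also rises; non-HDL cholesterol is the better choice and needs no new data

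*Protocol article*

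**What the plan says.** Under Measures, the Aim 3 row of Table 1 lists the child health outcomes item by item. Its lipid entries are total and HDL cholesterol: "total cholesterol, HDL cholesterol, liver function". The source is the EHR, at 0, 6 and 12 months. The line carries no 'for example', and no other lipid fraction appears in the table.

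Elsewhere the article is less specific:

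- The specific aims name "weight status, blood pressure, lipids, HbA1c, and liver function tests".
- The Specific Aim 3 section names "weight status, blood pressure (BP), lipids, HbA1c, and liver function tests".
- Medical record abstraction gives an illustrative list: "patient health outcomes (e.g., BMI, HbA1c, LFTs, cholesterol".
- Quantitative data places the labs under "a) metabolic labs, BP, BMI" and says that the growth models will "focus on significance of changes from baseline to post-treatment assessments".

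No section states which direction of change in total cholesterol counts as benefit. The Specific Aim 3 section sets the status of these outcomes: the study will "examine exploratory clinical effectiveness outcomes including family-level FI".

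**The concern.** Total cholesterol is HDL plus non-HDL cholesterol. On the ordinary reading, a rise in HDL and a fall in non-HDL are both favourable. A test of mean change in total cholesterol therefore adds a wanted rise to a wanted fall. If the programme improves both parts, the test sees only the net change. A small or null result on that line could then be read as no lipid effect, although non-HDL had fallen.

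What is at stake is modest but real. The article says that this trial will inform a fully powered Type 2 hybrid trial. An attenuated lipid line is poor information for choosing and sizing that trial's outcomes.

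**Working it through.** **The plan's own figure.** The article states no number for lipids. For Aim 3 generally, Power considerations reports more than 81% from simulated growth models at d of at least 0.20, with 60 families per clinic and 20% missing data. The serial correlation used is not given, so this cannot be reproduced exactly. A paired-change approximation serves as a background check:

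- n = 60 x 4 x 0.80 = 192.
- SD of change, in units of the baseline SD, = sqrt(2(1 - rho)), where rho is the correlation between baseline and follow-up.
- Power = Phi(d x sqrt(n) / SD of change - 1.96), two-sided alpha 0.05 (the article gives 0.05 without the side).
- At d = 0.20 this gives 0.79 for rho = 0.5, 0.81 for rho = 0.52 and 0.87 for rho = 0.6.

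The stated figure is therefore plausible for rho a little above 0.5, and it is not disputed. The steps below use rho = 0.5, for which the SD of change equals the SD.

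**Step 1: the identity.** Change in total = change in non-HDL + change in HDL. With assumed changes in mg/dL:

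| Non-HDL | HDL | Total | Share of the non-HDL fall not seen in total |
|---|---|---|---|
| -3 | +1 | -2 | 1/3 = 33% |
| -3 | +2 | -1 | 2/3 = 67% |
| -3 | +3 | 0 | 3/3 = 100% |

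The sizes are illustrative. The direction of the loss follows from the identity alone whenever HDL rises and non-HDL falls.

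**Step 2: power at the plan's effect size.** The article gives no lipid SDs. Assumed values are non-HDL 25 to 35 mg/dL, HDL 10 to 14 mg/dL, and a correlation r between the two changes of -0.3 to 0.3. Let each part improve by d = 0.20. At the middle values (30 and 12):

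- Change in total = -0.20 x 30 + 0.20 x 12 = -6.0 + 2.4 = -3.6 mg/dL.
- SD of total at r = 0: sqrt(30² + 12²) = sqrt(1044) = 32.3.
- d on total = 3.6 / 32.3 = 0.11.
- Power = Phi(0.111 x sqrt(192) - 1.96) = Phi(-0.42) = 0.34.
- At r = -0.3 the SD is 28.8, d is 0.125 and power is 0.41. At r = 0.3 the SD is 35.5, d is 0.10 and power is 0.29.
- HDL or non-HDL alone: Phi(0.20 x sqrt(192) - 1.96) = Phi(0.81) = 0.79.

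The pairs 25/10 and 35/14 give the same results, because the ratio of the SDs is 2.5 in each. Other pairings of the same values widen the range. For 25/14 at r = 0.3, d = 2.2 / 32.1 = 0.07 and power is 0.16. For 35/10 at r = -0.3, d = 5.0 / 33.4 = 0.15 and power is 0.55. All of these lie below 0.79.

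**Step 3: two boundary cases.**

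- *Full cancellation.* HDL must rise by as many mg/dL as non-HDL falls. At 30 and 12, a non-HDL fall of 6 mg/dL (d = 0.20) needs an HDL rise of 6 mg/dL (d = 6/12 = 0.50). Total change is then 0 and power on total is 0.05. Power stays at 0.79 on non-HDL and is about 1.00 on HDL.
- *HDL unchanged.* Total and non-HDL fall by the same amount. With the SD ratio at 2.5, power on total is 0.65 to 0.82 against 0.79 on non-HDL. Total cholesterol can then do slightly better or somewhat worse, depending on r. The loss described here arises when HDL moves.

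**The case against.** The strongest answer is that no information is lost. HDL stands in Table 1 as its own outcome, and nothing combines it with total cholesterol into a score. With non-HDL at -3 and HDL at +3, a reader sees total flat and HDL up by 3, and can work out that non-HDL fell. A reader might infer from the identity that a favourable lipid change as a whole can disappear. The documents do not support that: only the total-cholesterol line can cancel, and only with equal and opposite mg/dL changes. Nothing in the article suggests that this case is likely.

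Three other strong readings also fail.

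- *That the multiplicity adjustment is harmed.* Tests of change do not contradict one another because their desirable directions differ, and replacing one outcome by another leaves the number of tests unchanged.
- *That the aims and Table 1 contradict each other over lipids.* Total and HDL cholesterol are lipids, and a condensed article may sit beside a fuller list.
- *That further fractions should be abstracted.* The article does not show which fractions the EHR reports, or how often.

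It can also be said that derived variables belong in an analysis plan that is not shown. That is fair for a variable left open. Here Table 1 fixes total cholesterol as the listed outcome, and non-HDL is not listed. A value that can be recovered afterwards is not a prespecified outcome. This part of the objection lowers the severity but does not remove the point.

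**Conclusion.** The point holds in limited form. As listed, total cholesterol is an attenuated and ambiguous measure of benefit when HDL rises and non-HDL falls. With both parts improving by d = 0.20, its effect shrinks to about 0.10 to 0.13 and its power to about 0.29 to 0.41 (0.16 to 0.55 over the wider pairings of SDs), against 0.79 for either part. These values rest on assumed SDs, correlations and a baseline to follow-up correlation of 0.5. That the loss occurs when both parts improve does not depend on them.

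Severity is low. The outcomes are exploratory, lipids are one item among many, and no sample size or decision rule in the article depends on total cholesterol.

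**What to change.** In Table 1, and where the Quantitative data section refers to metabolic labs:

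1. Name non-HDL cholesterol (total minus HDL from the same blood sample) as the analysed outcome in place of total cholesterol.
2. Keep HDL as a separate outcome.
3. State the favourable direction of each: lower for non-HDL, higher for HDL. The effect-size statement in Power considerations is worded as an increase, so for non-HDL it should be read as a change in the favourable direction.

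Total cholesterol can still be reported descriptively. The cost is one derived variable from two values already planned for abstraction. It adds no blood test, visit or EHR field, and the number of tests stays the same.
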